
**Fig. 1 Fig1:**
[figure not shown]
PORTAL trial flowchart: patient inclusion and randomization, arms design, and statistical analysis. BMI, body mass index; PDAC, pancreatic adenocarcinoma; ITT, intention-to-treat; PP, per-protocol

**Fig. 2 Fig2:**
[figure not shown]
**a** Illustration of patient blinding in the postoperative setting; all wound dressings and drain sites are identical in patients who undergo both open and robotic pancreatoduodenectomy. **b** Illustration of trocar placement in robotic pancreatoduodenectomy; 1–3, robotic ports. C, camera port, A1––A3: assisting laparoscopic ports (utilized on individual patients basis)

### Operative technique: robotic pancreatoduodenectomy

The daVinci® Si or Xi Surgical System will be utilized for patients randomized to the RPD arm. The basic steps of the procedure are as follows: In the immediate preoperative setting, prior to anesthesia induction, subcutaneous deep venous thromboprophylaxis and intravenous antibiotics are administered, and the patient is placed in a supine position with split legs and the left arm in 90° abduction. After prepping and draping, access to the abdominal cavity is established with a supraumbilical or infraumbilical port, which accommodates the camera; the rest of the trocars are placed as follows (Fig. 2b): three robotic arm ports are placed in the left and right upper quadrant midclavicular line and the right subcostal anterior axillary line. A laparoscopic assistant port is also placed in the lower left quadrant midclavicular line; additional ports for further laparoscopic assistance and placement of liver retractor can also be utilized. The table is turned left at approximately 15° and the patient is placed in reverse Trendelenburg position to accommodate the docking of the robot.

A diagnostic laparoscopy is initially performed to exclude occult abdominal metastatic disease. Tissue dissection is initiated with access in the lesser sac by cutting the gastrocolic ligament, followed by mobilization of the hepatic flexure of the colon and performance of a Kocher maneuver for mobilization and exposure of the pancreatic head. Identification of the avascular plane between the posterior surface of the pancreatic head and the underlying inferior vena cava and right kidney follows. The fourth part of the duodenum is mobilized, and 40–50 cm of the jejunum is pulled through the gap under the mesenteric root and transected 10 cm from the ligament of Treitz. The inferior border of the pancreas is further dissected, the superior mesenteric vein (SMV) is visualized, and ligation of the gastrocolic trunk is performed. Attention is then turned to the superior pancreatic border, where the stomach is transected immediately proximal to the pylorus using a surgical stapler. The 8a lymph node is resected and sent to pathology, and posteriorly, the gastroduodenal (GDA) and right gastric arteries are also visualized and transected between Hem-o-lok clips (Teleflex Medical, Research Triangle Park, NC, USA). The anterior surface of the pancreas is exposed, and a tunnel is created under it; the pancreatic parenchyma is transected at the neck with diathermy or harmonic scalpel and sharply at the pancreatic duct. If indicated, frozen biopsies from the transected pancreatic margin are sent to pathology, and a 6-Fr catheter is placed in the pancreatic duct to secure visualization. The gallbladder is detached from the gallbladder fossa, and the hepatoduodenal ligament is then dissected to identify the common hepatic duct; this is transected above the junction with the cystic duct, close to the confluence. The specimen is positioned to the right of the PV/SMV for optimal exposure. The uncinate process is further mobilized with ligation of the inferior pancreatoduodenal arteries and veins, and the specimen is freed and placed in a collection bag, which is left temporarily within the abdomen.

The reconstruction phase starts with a single jejunal loop being passed in a retrocolic fashion through a small incision in the mesocolon on the right of the mesocolic vessels or through the tunnel under the mesenteric root. The pancreaticojejunostomy (PJ) is performed in an end-to-side fashion as a double-layer duct-to-mucosa anastomosis with interrupted 3/0 and 5/0 or 6/0 Prolene sutures for the outer and inner layer, respectively. Ten centimeters distally on the same jejunal loop, the hepaticojejunostomy (HJ) is constructed with running or interrupted 4/0 or 5/0 PDS or Prolene sutures, based on the diameter of the common hepatic duct. Lastly, the gastrojejunostomy is performed with single-layer running 3/0 V-loc (Covidien, New Haven, CT, USA) or 3/0 Vicryl sutures, or with an endostapler. If a pylorus-preserving pancreatoduodenectomy (PPPD) is decided, the subsequent duodenojejunostomy is performed in a similar fashion to the GJ. The abdomen is thoroughly inspected, and hemostasis is secured and two large-bore double-lumen surgical drains are placed in proximity to the PJ and the HJ. The specimen is extracted via the extended periumbilical trocar incision or a Pfannenstiel incision, which is closed in layers, and all trocars are removed, and skin incisions are sutured. Placement of wound catheters for postoperative pain control is optional.

Minor variations in the robotic surgical approach based on individual surgeon experience and preference, especially regarding the pancreatic and/or biliary anastomotic technique, will be discussed and accepted accordingly; documentation of any variations in patient records will be mandatory. Conversion rates from the robotic to the open procedure will be recorded in detail and assessed based on urgent and non-urgent conditions. Patients assigned in the robotic arm, who undergo a conversion procedure will be included as part of the robotic group in an intention-to-treat analysis.

### Operative technique: open pancreatoduodenectomy

In the control arm, patients will undergo an open pancreatoduodenectomy, which is the standard of care and has a long-standing safety record. A midline or right J-shaped subcostal incision is performed for access in the abdominal cavity. The operative steps are similar to the robotic approach in terms of tumor dissection, specimen removal, and anastomotic reconstruction. Since OPD volumes in participating centers are very high with quality results, wider surgical variations from individual surgeons are anticipated. These variations will be evaluated in advance and allowed accordingly, and they will also be documented in detail in patient records.

### Postoperative patient care

All participating centers are following a modified enhanced recovery after surgery (ERAS®) protocol, which focuses mainly on patient mobilization, pain management, and patient-directed oral intake and includes the following landmarks: removal of NGT on postoperative day and patient mobilization (POD) 1, clear fluids on POD 2, free fluids on POD4, and diet on POD5 as tolerated. Medical discharge will occur as a joint decision of the surgical team and the local community services that may need to be involved in the patient’s care as an outpatient. All patients are essentially declared fit for discharge as soon as functional recovery is achieved.

### Primary outcome measures

The primary outcome measure of the PORTAL trial for all participating patients is time to postoperative functional recovery, measured in days. The patients’ postoperative course will be evaluated daily by the nursing and medical staff and will be communicated to the study coordinators for documentation. Postoperative criteria that need to be fulfilled independently to achieve functional recovery status are as previously described [18]:
Discontinuation of intravenous or subcutaneous analgesia and preservation of adequate control levels (assessed by a pain score).Ability to maintain sufficient oral caloric intake as defined by the institutional dietetic services (no less than 50% of recommended dietary intake), without intravenous fluid support.Restoration of patient ambulation to an independent or preoperative level if mobility deficits were present.No clinical or biochemical signs of ongoing abdominal infection affecting the patient’s performance status: absence of fever and normalization of inflammatory markers (white cell count, procalcitonin, and/or C-reactive protein). Patients can be in oral antibiotics.

Additionally, in a sub-cohort of patients with pancreatic ductal adenocarcinoma assessed between the two study arms, the primary outcome will be the percentage of patients who achieve administration of adjuvant chemotherapy at 8 weeks postoperatively. The chemotherapy regimen will be decided by the oncology service on an individual basis and will not affect the comparison.

### Secondary outcome measures (Tables 1 and 2)

Multiple secondary outcomes will be compared within the trial. Intraoperative parameters will include operative time (from the first incision to skin closure) and estimated blood loss. Additionally, pathologic characteristics will also be studied, including tumor size and degree of differentiation, presence of perineural and/or lymphovascular invasion in PDAC, resection margin status, and number of harvested and infiltrated regional lymph nodes, as defined by the 8th edition of the American Joint Committee for Cancer [19]. Regarding the resection margin (R), it will be defined as R0 when tumor cells are detected > 1 mm from the margin, R1 when they are detected ≤ 1 mm from the margin, and R2 when there is macroscopically margin positivity. In the postoperative setting, the main secondary outcomes are complication rates as defined by the Clavien-Dindo classification [20] within 30 days and mortality within 90 days from operation. The trial will assess the occurrence of postoperative pancreatic fistula, biliary leak, chyle leak, delayed gastric emptying, bleeding, and surgical site infections (SSI) in both arms as defined by the International Study Group on Pancreatic Surgery [21–24] and the International Study Group in Liver Surgery [25], with a specific focus on the severe complications (Clavien-Dindo grade IIIa and higher). Subsequently, re-intervention (radiological, endoscopic, or surgical) and readmission rates will also be assessed. All interventions necessary for the treatment of participating patients in terms of management of potential complications are allowed. There are no limitations regarding patients’ care within this trial. All performed interventions will be documented in detail and assessed accordingly. Perioperative costs including postoperative hospitalization and readmissions within 30 days from the surgery will also be documented and evaluated. Lastly, quality of life (QoL) measurements will occur using patient questionnaires up to 3 months after surgery.

**Table 1 Tab1:** Trial progression portrayed as per Standard Protocol Items: Recommendation for Interventional Trials (SPIRIT) guidelines

Event	Preoperative setting (3 to 14 days pre-op)	Day of surgery	POD 1	POD 2	POD 3	POD 5	POD8/discharge day	POD 14	POD 30	POD 90	6 months post-op	1 year post-op	2 years post-op/time of death
Eligibility screening	X												
Informed consent	X												
Baseline characteristics	X												
Arm allocation	X												
QoL questionnaire (EQ-5D-5 L)	X						X	X	X	X	X	X	
Intraoperative outcomes		X											
Postoperative outcomes/secondary endpoints			X	X	X	X	X	X	X	X			
Primary endpoint assessment							X			X			
Recurrence-free and overall survival assessment													X

*pre-op* preoperative, *post-op* postoperative, *POD* postoperative day, *QoL* quality of life

**Table 2 Tab2:** Primary and secondary outcomes of the PORTAL trial

***Variable***	
**Primary outcomes** Time to functional recovery, *n* (days) Patients with PDAC who start adjuvant chemotherapy at 8 weeks, *n* (%)	
**Secondary outcomes** Estimated blood loss, ml Operative time, min Length of hospital stay, days 30-day morbidity, *n* (%) < Clavien-Dindo grade IIIa ≥ Clavien-Dindo grade IIIb 30-day mortality, *n* (%) 90-day mortality, *n* (%) 30-day readmission, *n* (%) Reoperation, *n* (%) Quality of life assessment Perioperative costs, $ In PDAC Resection margin status, *n* (%) Harvested lymph nodes, *n* Positive lymph nodes, *n* Recurrence, *n* (%) Recurrence site, *n* (%) Recurrence-free survival, month*s* Overall survival, months	

*OPD* open pancreaticoduodenectomy, *RPD* robotic pancreaticoduodenectomy, *PDAC* pancreatic adenocarcinoma

### Analysis of long-term outcomes in patients with pancreatic adenocarcinoma

The sub-cohort of patients with PDAC in the two arms will be followed up for a period of 2 years after surgery, or until their time of death within this period. During that time, the administration and type of systemic therapy will be documented; the main focus will be the recurrence-free survival (RFS) and overall survival (OS), defined as the time from surgery to the first radiological evidence of disease recurrence and death, respectively.

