### Randomization process (Fig. 1)

Eligible patients will be identified and discussed about the trial at the time of initial outpatient clinic assessment. Details will be provided to the patients about the goals and the structure of the trial and how it will affect the treatment approach. Recruited patients will be informed further in detail and will sign a written informed consent prior to treatment initiation, which can be revoked at any time. After signing the informed consent, all included patients will be randomized in a 1:1 ratio between robotic and open pancreatoduodenectomy using an online randomization module (IRT, Shanhu Health, Shanghai, China). Eligible patients will be variably randomized in equal proportions, with variable sizes blocks. After enrollment, they will be randomly stratified preoperatively based on [1] risk of developing a postoperative pancreatic fistula (POPF) using an externally validated model [17]: high risk (pancreatic duct diameter < 3 mm on preoperative CT at the pancreatic neck, and/or body mass index (BMI) > 25 kg/m^2^) versus low risk (pancreatic duct diameter ≥ 3 mm on preoperative CT at the pancreatic neck, and/or BMI ≤ 25 kg/m^2^) [2]; presence of endoscopic stenting for preoperative biliary drainage; and [3] diagnosis of pancreatic adenocarcinoma. Patient randomization and allocation between the two arms is performed with dedicated software (irtlite.irtone.com); after allocation, the patient details and allocated arm are typed into sealed envelopes by the randomization team, and the clinical nurse specialists deliver the envelopes to the appropriate surgical teams. The envelopes will be opaque and numbered with the patient trial ID number and will be opened by the responsible surgical team 1 day prior to surgery. Participating patients will be blinded to the procedure until postoperative day 5 or until functional recovery is achieved. Blinding will occur with the placement of identical wound dressings in all patients: on the presumed midline or J-incision and the placed trocars sites and extraction site incision in the RPD group and on the midline or J-incision and the presumed trocar sites and extraction site incision in the OPD group (Fig. 2a). Wound changes will occur as clinically indicated in an attempt to maintain patient blinding. This is a feasible approach that has been tested in previous randomized prospective trials [6, 18]. Unblinding of participating patients will be available as per their request; if a patient is accidentally unblinded, the event will be noted, and the patient will be excluded from the per-protocol analysis.

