### Statistical considerations and analysis

The main hypothesis in the PORTAL trial is that functional recovery of patients who undergo RPD is non-inferior to the one of patients who undergo OPD. Based on institutional historical data and information from retrospective series in the literature, the time to functional recovery in OPD is 10 days with a standard deviation of 2.5 days. Non-inferiority of functional recovery in RPD will be assessed with a non-inferiority (*δ*) margin of 10% or 1 day. With a one-sided test, a significance level of 5% (*α* = 0.05), and a power (1 − *β*) of 80%, the cohort for the trial is calculated to 200 patients (per-protocol (PP) group), using the PASS 11.0 software (NCSS, Kaysville, UT, USA) with a sample allocation ratio of 1:1 between the RPD and OPD groups. However, we anticipate a conversion rate in the RPD group of 10%, 3% incidence of occult abdominal metastatic disease in both groups, and 5% of patients to be lost to follow-up. Therefore, the final cohort will include 122 patients in each arm (intention-to-treat (ITT), Fig. 1). The main analysis will be conducted on the ITT group according to the randomized initial assignment of patients in each study arm at baseline. All enrolled patients from the ITT population who do not fulfill the aforementioned protocol violations will be included in the PP group. Additionally, patient characteristics of those who will be excluded from the PP analysis will be separately evaluated. Non-inferiority will be concluded if the lower bound of the 95% confidence interval (CI) for the difference between the two groups in time to functional recovery is not lower than − 1 day of the non-inferiority margin.

A second primary endpoint of the study is the percentage of patients with a diagnosis of pancreatic adenocarcinoma in each study arm, who will be fit for the initiation of postoperative adjuvant chemotherapy 8 weeks after the day of surgery. Institutional empirical data demonstrate that 50% and 75% of patients who undergo OPD and RPD, respectively, are eligible for adjuvant chemotherapy at 8 weeks, which is considered the optimal time for postoperative systemic treatment. With the same power and significance level as in the ITT group, 64 patients with pancreatic adenocarcinoma will be included in each arm to assess for the superiority of RPD.

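### Overall survival is counted from surgery but compared by randomised arm, so a PDAC patient who is randomised and never operated on has no defined survival time

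*Protocol article*

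**What the plan says.** Three parts of the protocol article bear on this point.

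- **Time origin.** The section on long-term outcomes in pancreatic adenocarcinoma has RFS and OS "defined as the time from surgery to the first radiological evidence of disease recurrence and death, respectively". Follow-up has the same origin: patients "will be followed up for a period of 2 years after surgery", or until death within that period.
- **Time of randomisation.** The section on the randomisation process states: "After signing the informed consent, all included patients will be randomized in a 1:1 ratio between robotic and open pancreatoduodenectomy". In Table 1 the row "Arm allocation" has its only mark in the column headed "Preoperative setting (3 to 14 days pre-op". The envelopes holding the allocation "will be opened by the responsible surgical team 1 day prior to surgery".
- **Analysis population.** The statistical section states: "The main analysis will be conducted on the ITT group according to the randomized initial assignment of patients in each study arm at baseline". It then applies both the ITT and the per-protocol group to primary and secondary outcomes. Table 2 lists RFS and OS among the secondary outcomes in PDAC. The survival comparison uses Kaplan-Meier estimates and the log-rank test.

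The article gives no start date or censoring rule for a patient who is randomised but has no operation. The losses it anticipates are conversion, occult metastatic disease and loss to follow-up; a cancelled operation is not named.

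**The concern.** An ITT comparison needs an outcome time for everyone randomised. A clock that starts at surgery gives one only to those who reach surgery. Consent can be revoked at any time, and in a wait of 3 to 14 days an operation can also be cancelled, refused, or pre-empted by progression or death. Such a patient belongs to the ITT set but has no time zero.

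The comparison that the definition allows is thus among operated patients, a group selected after randomisation, although the article calls its main analysis ITT. Patients lost before surgery may well have a poorer prognosis. The article makes RFS and OS the focus of PDAC follow-up, and its Discussion expects this analysis to settle the long-term oncological question. A survival comparison carrying that weight should be computable for every randomised patient.

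**Working it through.** The article states no hazard ratio, event count, power or sample size for OS or RFS, so there is no figure to reproduce. The check compares the stated rules and then sizes the consequence.

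**Consistency of the rules**
1. Start of OS: date of surgery.
2. Allocation: 3 to 14 days before surgery (Table 1).
3. Population: all randomised patients by assigned arm (ITT).
4. For a patient with rule 3 satisfied and no surgery date, rule 1 gives no value. The three rules cannot all hold for that patient.
5. A patient with occult metastases found at laparoscopy or laparotomy (3% anticipated) does have an operation date and is unaffected as regards OS.

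**Length of the gap**
- 3 / 30.44 = 0.10 month; 14 / 30.44 = 0.46 month.
- As a share of two years (730.5 days): 3 / 730.5 = 0.4%; 14 / 730.5 = 1.9%.

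**Number affected** (64 PDAC patients per arm from the article; the rate is an assumption)
- 2%: 64 × 0.02 = 1.3 per arm.
- 5%: 64 × 0.05 = 3.2 per arm.

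**Extreme case** (assumptions: true 2-year survival 50%, all losses in one arm, every lost patient would have died)
- None lost: 32/64 = 50.0%.
- 1, 2 or 3 lost: 32/63 = 50.8%, 32/62 = 51.6%, 32/61 = 52.5%.
- Standard error of a difference with 64 per arm at 50%: √(2 × 0.25 / 64) = 8.8 points. The largest shift, 2.5 points, is 2.5 / 8.8 = 0.28 of it.

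**Less extreme case** (assumptions: 2-year survival 45% if operated and 10% if not, the same in both arms)
- Shares not operated of 3% and 8%: (0.08 − 0.03) × (0.45 − 0.10) = 1.75 points, which an operated-only analysis would not show.
- Equal shares: 0 points.
- If operated patients differ between arms by D, and both arms have the same share u of unoperated patients with the same prognosis, the ITT difference is (1 − u) × D. At u = 5% this is 0.95 D.

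**The case against.** The strongest objection is that handling of unoperated patients usually belongs in the analysis plan or full protocol, neither of which is shown, and that a condensed article should not be faulted for its absence. That would settle the matter if the article were merely silent. It is not: it states a time origin and it states a population, and the two do not fit. What stands is that nowhere does it say unoperated patients are excluded. A reader might infer that exclusion is planned; it is only a consequence of the definition.

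Surgery is also a consistent origin here: the other postoperative outcomes run from the operation, and both arms are meant to receive one after a short wait. For operated patients the choice hardly matters, because a short and similar wait barely moves a log-rank test.

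A reader might go further and infer that cancellations depend on the arm, for instance through availability of the robot, or that waiting times differ between arms and so bias survival. The documents do not support this. The envelopes are opaque, the surgical team opens them one day before surgery, and patients are blinded until postoperative day 5 or functional recovery. For most of the wait neither knows the arm, and nothing in the text points to unequal waiting.

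Finally, moving the origin does not repair RFS. Its event is radiological recurrence, which a patient who was never resected cannot have. This stands, and it limits the correction mainly to OS.

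**Conclusion.** The point holds for OS in a narrow form. The surgical origin conflicts with the stated ITT comparison for any PDAC patient randomised but not operated on, and OS as defined describes operated patients.

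Its weight is small. It concerns a secondary endpoint with no stated hypothesis or sample size. The non-operation rate is not given; 2% to 5% is an assumption and means 1 to 3 of 64 patients per arm. Similar losses in both arms leave the between-arm difference essentially unbiased. Even the deliberately extreme case moves 2-year survival by at most 2.5 points, well inside the sampling error. It would be wrong to read this as evidence that the survival comparison is biased towards either arm. It is a mismatch of definition and population that is cheap to remove.

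**What to change.** - Define OS as time from randomisation to death from any cause, for every patient randomised in the PDAC stratum, analysed by assigned arm.
- Count the 2-year follow-up for OS from randomisation.
- Keep OS from surgery as a supportive analysis of operated patients.
- Leave RFS counted from surgery if it is labelled as an analysis of resected patients. An ITT version from randomisation would also need a rule on what counts as an event in patients never resected.

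The OS change is a short amendment to the definition and follow-up wording. The online randomisation module should already hold the date, and PDAC diagnosis is a preoperative stratification factor, so unoperated patients can be identified without a resection specimen. The cost is that reported OS times lengthen by about 0.1 to 0.5 month, which matters when they are set beside surgery-based series, and that vital status must be collected for the few patients who have no operation. No sample-size figure changes.
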